#### Intestinal-permeability assessment

Intestinal permeability will be evaluated by the serum quantification of claudin-3 and LPS biomarkers. From blood samples, serum will be obtained by centrifugation and stored at − 80 °C. The quantification of the biological markers will be performed by enzyme-linked immunosorbent assay (ELISA) according to the manufacturer’s instructions.

#### Sarcopenia

Sarcopenia will be determined following the European Consensus [25] considering muscle mass, muscle strength, and physical performance.

Muscle mass will be measured by the body composition assessment. DEXA (The GE Medical Systems Lunar Prodigy densitometer, Chicago, IL, USA) will be used for body-composition assessment. Fat and lean masses will be determined for the whole body and for body regions (trunk and limbs), as previously described [34]. Electrical bioimpedance (Biodynamics450®, Plainview, NY, USA) will be used to measure the percentage of fat, lean mass, and phase angle. Patients should be fasting for 4 h, not drink alcohol and/or caffeine, not have exercised in the last 12 h, not take diuretics the day before the test, not have a pacemaker in situ, and not be pregnant or menstruating. Patients will be questioned about the presence of significant diarrhea at the time of the examination to exclude the possibility of dehydration [35].

Muscle strength will be evaluated by the handgrip strength (dynamometry). Patients should be seated with their elbow flexed at 90° to hold the dynamometer (Jamar, Duluth, MN, USA) at its maximum strength for 3 s. There will be three repetitions with an interval of 1 min with the dominant hand. The highest strength will be recorded in kgF for classification [36].

Physical performance will be assessed through three different tests: the Five-times sit-to-stand test (FTSTS), the Usual Gait Speed test, and the Unipedal Stance test. The FTSTS test will be performed using a chair leaning against the wall. Initially, participants will be instructed to sit without assistance with their arms crossed in front of the body. If the patient demonstrates being able to perform this task they will be instructed to repeat the test five times, as close together as possible. The test performance will be measured by the time spent running the test [37]. To perform the Usual Gait Speed test the participant must walk a distance of 10 m in a straight line. The time taken to complete the course will be divided by the distance, providing the measure of the speed of the march (m/s). The test will be performed three times and the first and last 2 m will be excluded to discount the acceleration and deceleration phases. Participants will be asked to walk at their normal pace, even using walking aids and no incentive or instruction will be given in order to not influence the results [38]. A speed lower than 0.8 m/s will be considered as risk for sarcopenia [39, 40]. The Unipedal Stance test will be performed to evaluate the patient’s balance. Participants will be instructed to place their hands on their waist and raise one of their legs (chosen by the participant themselves) by flexing the knee and balancing on only one foot for a maximum of 30 s or until the individual becomes unbalanced. The test will be repeated three times and the longest time will be considered [41].

A blood sample will also be collected for the evaluation of testosterone, insulin-like growth factor 1 (IGF-1), and myostatin.

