### Statistical analysis

For the quantitative variables, the comparison between the values obtained before and after the intervention will be performed by the *t* test for parametric samples (or Wilcoxon’s signed-rank test if the data do not satisfy the assumptions for this test); for the qualitative variables, the McNemar test will be used.

In the comparison of treatments for the quantitative variables, a delta value will be computed (value before − value after); the delta values will be compared between interventions using the *t* test for independent samples (or the Mann-Whitney *U* test). Delta values can be adjusted by age and other covariates by analysis of covariance. It will be considered statistically significant if *P* < 0.05. Statistical analysis will be performed in SPSS 18.0.

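### The article defines gait speed as time divided by distance, which gives seconds per metre and contradicts the stated unit and the 0.8 m/s cut-off

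*Protocol article*

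**What the plan says.** In the Sarcopenia section of the protocol article, the gait test is described as follows: "the participant must walk a distance of 10 m in a straight line". The calculation is then given: "The time taken to complete the course will be divided by the distance, providing the measure of the speed of the march (m/s"). The test is done three times, and "the first and last 2 m will be excluded to discount the acceleration and deceleration phases". The result is classified by a threshold: "A speed lower than 0.8 m/s will be considered as risk for sarcopenia".

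The same section explains why the measure matters: "Sarcopenia will be determined following the European Consensus [25] considering muscle mass, muscle strength, and physical performance". Gait speed is one of three physical-performance tests, with the sit-to-stand and one-leg stance tests. Under Outcomes, the last secondary outcome is change in sarcopenia parameters, and physical capacity is one of the measures listed there. Under Statistical analysis, each quantitative variable is compared between arms through its change: "a delta value will be computed (value before − value after"). No other section gives a different formula for gait speed.

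**The concern.** The stated operation and the stated unit exclude each other. Dividing seconds by metres gives s/m, the reciprocal of speed, so a high value means a slow walker. The cut-off reads the scale in the opposite direction, with low values taken as the sign of risk. An evaluator who followed the sentence as printed would pass slow walkers and flag fast ones.

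The change score would suffer too. A patient who walks faster at week 24 has a lower pace, so before minus after comes out positive instead of negative. Read as a speed, that improvement would look like a decline. The reciprocal is also not linear, so reversing the sign afterwards would not recover the change in m/s.

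A second, smaller gap lies next to the first. The only distance given for the course is 10 m, but parts of it are left out of the measurement, and the text does not say which distance enters the calculation. Swapping numerator and denominator would not settle that.

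**Working it through.** **Inputs**, all from the Sarcopenia section unless noted: course length 10 m; 2 m left out at each end; formula time ÷ distance; risk flag for values below 0.8; change defined as before minus after (Statistical analysis).

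**Units.** Time ÷ distance is in s/m. Distance ÷ time is in m/s. Only the second matches the unit and the word speed in the text, so the stated formula does not reproduce the stated quantity.

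**Effect on the flag.** For a true speed v over a distance D, the time is t = D/v. The formula as written gives t/D = 1/v, whatever D is, provided that D is the distance actually timed. The flag 1/v < 0.8 is then equivalent to v > 1/0.8 = 1.25 m/s.

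| True speed (m/s) | Time over 10 m (s) | Time ÷ distance | Flagged as written | Flagged with distance ÷ time |
|---|---|---|---|---|
| 0.5 | 20.0 | 2.00 | no | yes |
| 0.7 | 14.29 | 1.43 | no | yes |
| 0.8 | 12.5 | 1.25 | no | no |
| 1.0 | 10.0 | 1.00 | no | no |
| 1.25 | 8.0 | 0.80 | no | no |
| 1.3 | 7.69 | 0.77 | yes | no |
| 1.4 | 7.14 | 0.71 | yes | no |

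All walkers below 0.8 m/s are missed and all above 1.25 m/s are flagged. Between 0.8 and 1.25 m/s the two formulas agree that there is no flag. With distance ÷ time, the flag catches walkers who need more than 10/0.8 = 12.5 s over 10 m, or more than 6/0.8 = 7.5 s over 6 m.

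**Effect on the change score.** Take two illustrative patients who each gain 0.2 m/s.

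- From 0.7 to 0.9 m/s: the change in speed is 0.7 − 0.9 = −0.2. As written it is 1/0.7 − 1/0.9 = 1.429 − 1.111 = +0.317.
- From 1.1 to 1.3 m/s: the change in speed is 1.1 − 1.3 = −0.2. As written it is 1/1.1 − 1/1.3 = 0.909 − 0.769 = +0.140.

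The sign flips, and equal gains in speed become unequal changes in pace, the first 0.317/0.140 = 2.3 times the second. A between-group comparison of mean changes is therefore not the same analysis with the sign reversed.

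**Timed distance.** If 10 m is the whole walkway, the measured part is 10 − 2 − 2 = 6 m. The time and the distance in the formula must refer to the same stretch.

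**The case against.** The strongest reply is that this is a slip in one phrase. The test is called a speed test, the result is labelled m/s, and low values are treated as the risk. All three point to distance over time. Literal use would also give implausible records: someone who takes 20 s over 10 m would be entered at 2.0 m/s. This argument stands in large part. The article does not show what the evaluators calculate, so every consequence above is conditional on the sentence being applied as printed. What remains is that the only formula in the document is wrong and nothing elsewhere corrects it.

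A reader might infer that the sarcopenia classification is simply reversed. It is not, even on a literal reading, because the band from 0.8 to 1.25 m/s is treated alike by both formulas.

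A reader might also infer a further error of 10/6 = 1.67, or 67%, from combining a 6 m time with 10 m; a true 0.5 m/s would then become 10/(6/0.5) = 0.83 m/s and pass the cut-off. Nothing in the text says that the two are combined. That figure also requires distance over time, so it cannot occur together with the inversion. The text leaves the distance unstated, and a condensed article may well leave that to an operating manual. It is worth settling only because the sentence has to be rewritten anyway.

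Finally, the reach is narrow. Gait speed is one of three tests within one of three domains of sarcopenia. The secondary outcome that holds it is also assessed by body composition and blood markers, and the same formula would be applied in both blinded arms. This limits the weight of the point but does not make the formula right.

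**Conclusion.** The definition is wrong as written: it yields s/m and contradicts both its own unit and the cut-off in the same paragraph. If it is applied literally, walkers below 0.8 m/s go unflagged, those above 1.25 m/s are flagged, and the change in gait alters in sign and scale. These figures assume that the distance in the formula is the distance timed.

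The conclusion is about the text. The article does not support the stronger claims that recorded values are wrong or that patients have been misclassified. The primary outcome (elastography) and the sample size are unaffected; the effect is confined to one component of a secondary outcome. This is a minor point that should be corrected.

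**What to change.** Replace the sentence with a definition of this kind: gait speed (m/s) equals the timed distance in metres divided by the time in seconds over that distance. Name the timed distance in the same sentence. It is 6 m if the first and last 2 m belong to the 10 m course, which the sponsor should confirm. State that the same formula applies at baseline and at week 24.

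The Trial status section reports that 45 patients had started the study protocol, so baseline gait values probably exist. Check how they were derived, and recalculate from raw times only where another formula or distance was used. A blanket recalculation is not justified, since the article shows neither that values were computed wrongly nor that raw times were kept in the database.

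The cost is one corrected sentence and a check of existing records. No new measurement is needed.

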#### Physical-activity assessment

The International Physical Activity Questionnaire – Short Form (IPAQ) will be applied to evaluate the weekly time spent in physical exercise.

#### Cardiovascular-risk assessment

Cardiovascular risk will be estimated by the Framingham Risk Score [42] and the Atherosclerotic Cardiovascular Disease (ASCVD) risk calculator [43].

All data will be included in the database filled out by the researchers, as well as in a physical agenda to log the attendance frequency of the participants. The patients will be contacted to be reminded about the guidelines and to confirm the visits. Subjects who discontinue treatment will also have their data treated at the end of this study.

#### Laboratory assessment

Laboratory assessment will consist of a liver function test (aspartate aminotransferase, alanine aminotransferase, gamma glutamyl transferase, bilirubin, alkaline phosphatase), a lipid profile (triglycerides, total cholesterol, HDL-cholesterol, non-HDL cholesterol, and LDL-cholesterol) and the levels of other relevant indices such as CRP, insulin, glucose, glycated hemoglobin, HOMA-IR, albumin, creatinine, and a blood count. Serum will be obtained by centrifugation and stored at − 80 °C. Quantification of the biomarkers will be performed by ELISA according to the manufacturer’s instructions.

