### Eligibility criteria

Inclusion criteria: adult subjects diagnosed with NASH, with or without fibrosis, by liver biopsy.

Exclusion criteria: patients with human immunodeficiency virus, hepatitis B virus or hepatitis C virus infection; a significant intake of alcohol; cirrhosis; pregnancy; liver transplantation; supplements and foods with probiotics; use of immunosuppressant, antibiotic, and corticosteroid drugs, and valproic acid and amiodarone, and with any other chronic inflammatory diseases.

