#### Clinical evaluation

The data collection protocol includes demographic data, clinical diagnosis and diagnostic methods, medications in use, alcohol consumption, smoking status, and blood pressure measurement. In addition, details of the disease diagnosis (liver biopsy and transient elastography) are recorded.

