#### Scores

The NAFLD Fibrosis Score, APRI Score and Fatty Liver Index [31–33] are useful tools for the diagnosis and monitoring of patients with NAFLD. The NAFLD Fibrosis Score is based on the following parameters: age, Body Mass Index (BMI), whether type-2 diabetes mellitus or impaired fasting glucose, alanine aminotransferase, aspartate aminotransferase, and platelet and albumin levels, while the APRI Score includes the aspartate aminotransferase level and platelet count. The Fatty Liver Index diagnoses fatty liver using laboratory parameters (alanine aminotransferase, aspartate aminotransferase, gamma glutamyl transferase, glucose, insulin, triglycerides, cholesterol levels), and clinical (gender, age, alcohol intake) and anthropometric (waist circumference, triceps, biceps, subscapular and supra-iliac skinfolds) findings. The scores will be calculated via an online calculator (MDCalc.com).

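### The general change-score comparison covers insulin and HOMA-IR without setting insulin-treated patients apart, although their changes in these two indices do not measure insulin resistance

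*Protocol article*

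**What the plan says.** - **Measurement.** Protocol article, Laboratory assessment, lists indices "such as CRP, insulin, glucose, glycated hemoglobin, HOMA-IR, albumin, creatinine, and a blood count". Nothing separates patients by diabetes treatment.
- **Eligibility.** Protocol article, Eligibility criteria, admits "adult subjects diagnosed with NASH, with or without fibrosis, by liver biopsy". The drug exclusions are "use of immunosuppressant, antibiotic, and corticosteroid drugs, and valproic acid and amiodarone". Neither insulin nor diabetes is excluded.
- **Diabetic patients are expected.** The Background describes a strong association between the disease and diabetes. The Scores section uses as a score input "whether type-2 diabetes mellitus or impaired fasting glucose".
- **Analysis.** Protocol article, Statistical analysis, gives one rule for quantitative variables: compute before minus after, and "the delta values will be compared between interventions using the" independent-samples t test or the Mann-Whitney test. Covariance adjustment for age and other covariates is optional.
- **Medication data.** The Clinical evaluation section records "clinical diagnosis and diagnostic methods, medications in use, alcohol consumption", so insulin users can be identified.
- **Outcome rank.** The Outcomes section does not name insulin or HOMA-IR. The nearest entry is the secondary outcome on metabolic-syndrome components, assessed partly by laboratory tests.

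**The concern.** HOMA-IR is built from the product of measured insulin and glucose. It indexes insulin resistance only when the insulin is the patient's own. In an insulin-treated patient the measured value can follow the dose, product and timing of injections at each visit. The before-minus-after difference then says little or nothing about insulin resistance, and the same applies to insulin taken alone.

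Two things are at stake. The first is validity: these patients' changes enter the between-arm comparison without measuring what it is meant to compare. The second is precision: in a trial of 46, a few patients on a higher and more variable scale can dominate the variance of the raw change and hide a real difference in the others.

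**Working it through.** **No figure to reproduce.** The article states no effect, variance or power for insulin or HOMA-IR. Its sample size of 46 is for the primary outcome and is used here only for the number of patients: 46 × 0.9 = 41.4, taken as 42, or 21 per arm with equal arms.

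**Step 1: what the text fixes.** Eligibility admits insulin users, the laboratory list measures insulin and HOMA-IR in whoever is enrolled, and the analysis rule covers quantitative variables without exception. Read together, an insulin-treated patient's change enters the comparison.

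**Step 2: simulation on the HOMA-IR scale.** All inputs except the 21 per arm are assumptions:
- median HOMA-IR 4, between-person log-SD 0.5;
- visit-to-visit log-SD 0.25 in non-users;
- in users, values 2 times higher with visit log-SD 0.5 (mild) up to 4 times higher with 0.7 (severe);
- a true 25% reduction in non-users on probiotic, none in users;
- delta = before − after on the raw scale, two-sided 5%, 4,000 trials per setting.

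Power, mild to severe setting:

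| Share of users | t test, users in | t test, users out | Mann-Whitney, users in | Mann-Whitney, users out |
|---|---|---|---|---|
| 5% | 38% to 24% | 53% | 52% to 51% | about 57% |
| 10% | 27% to 12% | about 50% | 45% to 43% | 55% to 53% |
| 20% | 15% to 6% | 46% | 32% to 30% | 48% |

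Repeat runs agree to within about 2 percentage points (at 10% users, for example, 28% to 11% for the t test with users in). At 10% users, 0.10 × 42 = 4.2, so about four patients are involved.

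**Step 3: a second model as a cross-check.** Change scores have SD 1 in non-users and SD r in users, with a true difference of 1.0 SD in everyone. That is about what 21 per arm detects with 90% power: (1.96 + 1.28) × √(2/21) = 1.00. With k users among 42, their share of the variance is k·r² / (k·r² + 42 − k). For k = 4:
- r = 3: 36 / (36 + 38) = 49%; t-test power 67%, Mann-Whitney 78%.
- r = 10: 400 / (400 + 38) = 91%; t-test power 24%, Mann-Whitney 72%.

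With no users, simulated power is about 88% (t test) and 86% to 87% (Mann-Whitney). Leaving out the four users (19 per arm) gives Φ(√(19/2) − 1.96) = Φ(1.12) = 87%. The few patients lost cost little; keeping them costs more, under either test.

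**Step 4: false positives.** With no true effect and users kept in, type I error was 1.6% to 4.4% (t test) and 4.2% to 5.4% (Mann-Whitney) in the first model, and 2.3% to 4.8% (t test) in the second. The test does not reject too often.

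**The case against.** **The text does not say that HOMA-IR is analysed in every patient.** That is fair: this is a condensed article, and a full protocol or analysis plan could restrict these indices. What stands is that the article does not defer the point. It states a rule for quantitative variables, and that rule as written includes insulin users.

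**A reader might infer that a few patients swamp the comparison and most of the power is lost.** That describes the t test only. The plan provides Mann-Whitney as an alternative, and grossly skewed changes should lead to it: with a normality test in each arm as an assumed trigger, normality was rejected in 84% to 97% of trials at 10% users. Under Mann-Whitney the relative loss at 10% users is (55 − 45)/55 = 18% to (53 − 43)/53 = 19%, about a fifth. The fallback tames outliers, but it does not turn these patients' changes into a measure of insulin resistance. Nor would the optional covariance adjustment.

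**A reader might infer that spurious differences are created.** An imbalance can move a single trial's estimate either way, but the null runs show no inflation of type I error.

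**A reader might infer that a stated insulin-resistance outcome is damaged.** None is stated. These are two entries in a list of laboratory indices.

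**The size is all assumption.** This is correct. The number of insulin users may be zero, and how much injected insulin registers depends on the assay, which the article does not describe in that respect.

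**Conclusion.** The point holds in a limited form. As written, the general change-score rule takes in insulin and HOMA-IR values from insulin-treated patients, in whom these changes do not measure insulin resistance. If such patients are enrolled, the comparison loses validity and some power. At an assumed 10% of users and a 25% true effect in the others, t-test power is about 12% to 28% instead of about 50%, and Mann-Whitney power about 43% to 46% instead of 53% to 55%. At 5% users the Mann-Whitney loss is about 5 to 6 points; at 20% it is 16 to 18 points. With no users there is no effect.

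The harm is uninterpretable changes and reduced power, not false positives. It is limited to two secondary laboratory indices. The primary elastography outcome, the named secondary outcomes, glucose and glycated hemoglobin are not in question.

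**What to change.** Add to the statistical analysis section, before unblinding:
- The between-arm comparison of insulin and HOMA-IR is made in patients not using insulin at baseline, identified from the recorded medications.
- The number left out is reported per arm.
- Two sensitivity analyses are given: all patients, and patients who start insulin during follow-up also left out.
- Glucose and glycated hemoglobin are analysed in all patients.

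The main restriction should rest on baseline use. Removing patients who use insulin at either visit would condition on an event after randomization that the glycaemic response to treatment could influence, which is why that version belongs in a sensitivity analysis.

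The cost is a few sentences and no new data. The comparison uses slightly fewer patients, and its result for these two measures applies only to patients not on insulin at baseline. Fixing the subset before unblinding also prevents a choice made after seeing the results.

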#### Nutritional assessment

The anthropometric assessment will include the measurements of weight and height for calculating BMI, waist circumference between the twelfth rib and the iliac crest with an inextensible fiberglass tape measure, and tricipital, bicipital, subscapular and supra-iliac skin folds using a Lange® adipometer [33].

Dietary intake will be checked by 3-day diet record, describing the foods eaten for three non-consecutive days (two weekdays and one weekend day). The records will be calculated using the NutriBase® software, 2007. Evaluation of total, insoluble, and soluble fiber intake will be calculated through the data of the spreadsheet developed by Schakel et al. [44].

